#### Secondary outcome measures

The ability of the microbiome signature to predict 6 month PFS, 2 year PFS, overall response rate, median PFS and median overall survival (OS) in cohorts 1–6.The ability of the microbiome signature to predict for 1 and 2 year relapse after resection of high risk melanoma or renal cancer in cohorts 7–9. (Table 2 and Fig. 2)

**Table 2 Tab2:** Cohorts 7–9 – Adjuvant disease cohorts and defined standard of care ICI-containing treatment regimens

Cohort	Disease	Regimen	Primary outcome measure
Cohort 7	Resected AJCC stage 3 or 4 melanoma	Anti-PD-1 monotherapy (nivolumab or pembrolizumab)	1 year & 2 year RFS
Cohort 8	Resected renal cancer	Durvalumab	1 year & 2 year RFS
Cohort 9	Resected renal cancer	Durvalumab+tremelimumab	1 year & 2 year RFS

To compare oral and gut microbiome findings and their association with treatment efficacy.To correlate microbiome findings with incidence and characteristics of CTCAE V5-defined Grade > 3 IrAEs in all enrolled patients, and any association with response to immunosuppressants.To correlate microbiome findings with aspects of pre-existing patient characteristics and behaviour including but not limited to diet, smoking history, BMI, use of antibiotics, steroids, PPIs, NSAIDs and probiotics.To compare the microbiome signature of cancer patients with a household control group of people who are not known to have cancer.To retain a library of biological samples with linked patient data for future research.

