### Assessments on study

Patients will be followed up during their routine clinic visits, with study-specific data collection at time points approximating to baseline (pre-treatment), 6–8 weeks, 12 weeks, 3 monthly until 1 year, then 6 monthly thereafter until and including disease progression, or relapse, or study termination.

Immune-related adverse events (IrAEs) will be recorded at each clinic visit.

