### Treatment for disease progression or relapse

Treatment for disease progression in the metastatic setting and for relapse on or after adjuvant therapy is at the Investigator’s discretion and local practice. Patients deriving clinical benefit from palliative therapy with ICIs in the presence of progression determined by RECIST 1.1 may continue on treatment beyond progression at the investigator’s discretion. However, no further formal RECIST reporting will be required.

For patients with advanced disease, the first RECIST progression date will be used for measuring PFS in this study. For adjuvant patients, the first date of relapse will be used for measuring RFS.

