### Collection of clinical data

No additional clinic visits or consultations are required for this study over and above standard of care. Cancer patients will be followed up during their routine clinic visits/consultations, with study data collection time points approximating to baseline (pre-treatment), 6–8 weeks, 12 weeks, 3 monthly up to 1 year, then 6 monthly thereafter until disease progression or relapse, up until the study closure date. Additional clinic assessments may be required as per local practice but study data collection will only be required if the assessment is for first disease progression/relapse. Details of data collected at each visit is available in Additional file 3.

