### Statistical analysis methods

The main clinical outcome to be correlated with the gut microbiome metagenomic data will be PFS in patients with advanced disease. The hypothesis to be tested is concerned with the effect of the microbiome profile on PFS. There will be an interim analysis evaluating the effect of the biomarkers on 6-month PFS while the main analysis will assess the effect on 1 year PFS.

All primary analyses will be based upon a regularised logistic regression with the false discovery rate being controlled at 0.05 and the regularisation parameter being estimated using cross-validation.

Two sensitivity/exploratory analyses will be conducted to assess the robustness of the composition of the microbiome signature and its exact effect on the clinical outcome. The first will estimate the effect of the biomarkers on the complete survival curve (up to the particular follow-up) using a Cox model. The second will use a random forest classifier to evaluate the effect of the microbiome profile on the PFS.

Regularised logistic regression will be also used for associating the gut microbiome with a number of secondary endpoints, such as the incidence of adverse events. The secondary outcomes which depend upon the complete survival curve such the median PFS and the median OS will be correlated to the microbiome signature using a Cox model.

The logistic regression and Cox model-based analyses are likely to be conducted in R using the glmnet package. The random forest classifier will likely be fitted using the random Forest R package. A detailed statistical analysis plan will be produced before the final data base lock or before any interim analysis is performed (as appropriate).

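### Severe immune toxicity is modelled as a yes/no outcome while scheduled data collection ends at progression, so a signature that predicts PFS can show a distorted association with toxicity

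*Protocol article*

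**What the plan says.** Statistical analysis methods assigns regularised logistic regression to the task of "associating the gut microbiome with a number of secondary endpoints, such as the incidence of adverse events". Cox modelling is kept for a different group: "The secondary outcomes which depend upon the complete survival curve such the median PFS and the median OS". Toxicity is thus placed on the logistic side, and the section states no window, offset or censoring rule for it.

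Secondary outcome measures defines the toxicity outcome as "incidence and characteristics of CTCAE V5-defined Grade > 3 IrAEs in all enrolled patients", again without a time horizon.

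On capture, Assessments on study says "Immune-related adverse events (IrAEs) will be recorded at each clinic visit", and runs study data collection "then 6 monthly thereafter until and including disease progression, or relapse, or study termination". Collection of clinical data agrees: "then 6 monthly thereafter until disease progression or relapse, up until the study closure date". It adds that data from extra clinic assessments are needed only where the assessment is for first progression or relapse.

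Treatment can outlast this. Under Treatment for disease progression or relapse: "Patients deriving clinical benefit from palliative therapy with ICIs in the presence of progression determined by RECIST 1.1 may continue on treatment beyond progression".

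**The concern.** A logistic model of a yes/no IrAE gives equal standing to a patient who progressed at 2 months without an IrAE and one who was followed progression-free for 12 months without one. The first was observed for a sixth of the time. If the signature predicts PFS, as the primary objective supposes, patients with a favourable signature are observed longer and have more opportunity to record an IrAE, even when the hazard of toxicity is the same in both groups.

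The distortion has a direction: towards more toxicity in patients with better PFS. It can create an association where the signature has no effect on the rate of toxicity. It can also hide a real one in which the favourable signature goes with less toxicity. Evaluating the link between microbiota and toxicity is a stated secondary objective, and the outcome is taken over all enrolled patients (up to 1800), where even a modest bias becomes detectable.

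**Working it through.** The article gives no figure for the toxicity analysis, so there is nothing to reproduce; Table 3 concerns power for PFS. The calculation below is an illustration.

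**Inputs from the article.** 1-year PFS of 42%, 50% and 47% for the three indicative cohorts (Sample size); severe or life-threatening toxicity in up to 50% of treated patients (Background); first stage 6 × 50 = 300 patients (Interim analysis); maximum 1800 patients (Study design).

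**Assumptions.** Exponential PFS; the same IrAE hazard whatever the signature; IrAEs counted only before progression; a nominal two-sided 5% test of one unpenalised predictor.

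**Closed form, binary signature split 50:50, average 1-year PFS 47%.** With progression hazard λ = −ln(1-year PFS), IrAE hazard h and window τ, the probability of an observed IrAE is

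p = h/(h+λ) × [1 − exp(−(h+λ)τ)].

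Take 1-year PFS of 35% v 59%, h = 0.52 per year, τ = 1 year:

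- λ₀ = −ln 0.35 = 1.050; λ₁ = −ln 0.59 = 0.528; PFS hazard ratio 0.528/1.050 = 0.50.
- p₀ = 0.52/1.570 × (1 − e^−1.570) = 0.262.
- p₁ = 0.52/1.048 × (1 − e^−1.048) = 0.322.
- Odds ratio = (0.322/0.678)/(0.262/0.738) = 1.34, although the IrAE hazard is identical in the two groups.

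If IrAEs can occur only in the first 3 months (h = 1.6 per year, τ = 0.25 year), the same formula gives p₀ = 0.2925, p₁ = 0.310 and an odds ratio of 1.09.

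**Spurious odds ratios at about a 30% IrAE rate, 1-year window**

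| 1-year PFS | Constant hazard | Four-fold hazard in first 3 months | First 3 months only |
|---|---|---|---|
| 40% v 54% | 1.18 | 1.11 | 1.05 |
| 35% v 59% | 1.34 | 1.20 | 1.09 |
| 25% v 69% | 1.75 | 1.42 | 1.18 |

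Under constant hazard the three rows rise to 1.32, 1.61 and 2.45 with a 2-year window.

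**Simulated false-positive rates of the unadjusted logistic comparison (2000 runs, 1-year window)**

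| 1-year PFS | Constant hazard, N=50 / 300 / 1800 | First 3 months only, N=300 / 1800 |
|---|---|---|
| 40% v 54% | 5.5% / 10.9% / 36% | 5.9% / 7.9% |
| 35% v 59% | 6.0% / 20.6% / 80% | 6.3% / 12.5% |
| 25% v 69% | 11.1% / 56.9% / 100% | 9.5% / 34.7% |

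With equal PFS (47% v 47%) and constant hazard the rate is 4.7-4.8%, so the excess comes from unequal observation.

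**Do the alternatives remove it?** In the 35% v 59% constant-hazard case, an exposure-adjusted rate rejects in 4.2%, 4.6% and 5.4% of runs at N=50, 300 and 1800. Logistic regression with everyone observed for the full year regardless of progression gives 4.2%, 5.6% and 5.6%.

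**Continuous signature.** With a PFS hazard ratio of 0.7 per SD, 1-year PFS of 42-50% and a 12-month IrAE risk of 30-50%, the odds ratio per SD is 1.13-1.19 under constant hazard and the rejection rate at n=300 is 14-29%. With IrAEs only in the first 3 months the figures are 1.04-1.06 and 6-8%. The cause-specific Cox hazard ratio is about 1.00. A crude rate per patient-time was itself biased (0.92-0.98) when toxicity came early, which is why Cox is preferred to a simple rate.

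**The case against.** A reader might infer that every PFS-predictive signature must come out as a false predictor of toxicity. The documents do not support that. The size turns on IrAE timing, follow-up window, strength of PFS prediction and sample size, none of which the article fixes for this analysis. With early toxicity, or at 50 patients per cohort, the effect would often go unnoticed.

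Four further objections have weight.

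- **The error rates are not those of the planned procedure.** They come from an unpenalised single-predictor test; the plan is a cross-validated regularised model, with false discovery rate control stated for the primary analyses. This stands: the rates are illustrative. The dependence of observation time on PFS does not go away with penalisation.
- **The yes/no outcome can be a legitimate quantity.** If everyone is followed to progression or a fixed horizon, it is the cumulative incidence of an IrAE before progression. Where treatment stops at progression, fewer IrAEs in early progressors is partly real, through lower exposure. This stands too: the bias concerns toxicity per unit of time at risk. The objective asks only about association, so a conclusion that beneficial bacteria cause harm would be the reader's own. But the article sets no horizon, so the meaning of the yes/no outcome is left open.
- **Capture after progression is not settled.** The sentence on recording IrAEs at clinic visits has no stated end. The sampling trigger under ICI treatment is not limited to the period before progression. Study design speaks of data before, during and after treatment for up to 5 years, and visit content is in Additional file 3, which is not shown. If IrAEs were captured over a common window for everyone, the problem would largely disappear. As written, the scheduled collection points stop at progression.
- **A detailed SAP is promised.** It could set a window or a censoring rule. The article nevertheless already names the model class for toxicity and separates it from the outcomes given a Cox model.

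**Conclusion.** The point holds as a conditional bias in a secondary analysis. Followed as written, the plan ties IrAE observation time to PFS and then ignores observation time in the model. A PFS-predictive signature can therefore show a spurious or distorted association with toxicity per unit of time at risk, towards more toxicity in patients with better PFS.

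The size ranges from negligible to substantial. The constant-hazard and first-3-months cases bracket the main uncertainty, IrAE timing. The distortion is hard to detect at cohort level in the first stage, and can be marked in a pooled analysis near 1800 patients. The IrAE hazard shapes, PFS contrasts and signature distribution are assumptions; the PFS levels, the upper toxicity rate of 50% and the sample sizes of 50, 300 and 1800 come from the article. The change should be made, but the documents do not justify saying that a false toxicity finding is certain.

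**What to change.** 1. Analyse time from the start of checkpoint inhibitor treatment to first severe IrAE with a penalised cause-specific Cox model, censoring at the end of IrAE observation. The glmnet Cox fit is already planned for other outcomes.
2. Report cumulative incidence with progression and death as competing events. Say that this curve describes absolute risk before progression, not susceptibility per unit of time at risk; it will still differ between signature groups if PFS does.
3. Keep logistic regression only for a fixed early window in which IrAEs are captured whether or not the patient has progressed.
4. State whether IrAEs after progression are collected, and confirm that onset dates are recorded. The article does not say, and visits become 6-monthly after the first year.
5. Reconcile the severity threshold first: the abstract uses grade 3 or above, while Secondary outcome measures, ICI treatment and Biological sample collection use above grade 3.

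The cost is small: plan wording, some added analysis work and possibly one date field. If IrAEs after progression are not now captured, item 3 would need further data collection; items 1 and 2 would not.

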### Interim analysis

In the first stage of this study, a total of 50 patients will be recruited in each of the first 6 cohorts with specific types of advanced cancer: melanoma, renal cancer and NSCLC and followed for a minimum of 6 months. The outcomes of this first stage will determine on-going enrolment and any requirement to amend the protocol.

### Ethics and dissemination

#### Research ethic approval

The study will be performed in accordance with the spirit and the letter of the declaration of Helsinki, the conditions and principles of Good Clinical Practice, the protocol and applicable local and national regulatory requirements and laws.

#### Dissemination of results

Ownership of the data arising from this study resides with the study management group (SMG). The main study results will be presented at national and international conferences and published in a peer-reviewed journal, on behalf of all collaborators. All participating sites and Investigators will be acknowledged in publications and presentations. In addition, patients and participants who have consented to receive updates on study progress and results, will be provided with appropriate updates and a summary of the results in lay terms.

## Discussion

ICIs are revolutionising cancer management, with growing evidence of activity across a wide spectrum of cancers. However, generally the minority of patients treated with these high-cost drugs benefit, while IrAEs can be devastating. There is an urgent need to identify biomarkers that are predictive of treatment response, resistance and toxicity, and emerging data points to the gut microbiome as an important influencer of these outcomes [7, 11].

So far, identification of specific responsible bacterial taxa has been inconsistent between published studies, which likely reflects small patient cohorts studied, as well as limitations in analytical methodologies used. By culturing and metagenomic sequencing stool sample bacteria, our group has identified a unique consortium of bacteria, which appears to be predictive of response to ICIs across all key published series as well as our own melanoma patient series [27].

MITRE is a large-scale, multicentre study on the NIHR portfolio, which will generate the largest cancer microbiome dataset of its kind. The main objective of the MITRE study is to prospectively evaluate and validate a gut microbiome ‘signature’ which can predict ICI efficacy in patients with advanced cancer, as well as its role for predicting severe ICI-induced toxicity. Collection of associated blood and tissue samples will provide a rich resource with which to interrogate immune and genomic factors that may explain the functional interplay of the microbiome and our immune system.

A number of clinical studies have demonstrated that therapeutic microbiome manipulations can be used to treat infections and autoimmune diseases; and going forward this approach may be feasible for cancer patients receiving immunotherapy. Indeed recently, as proof of principle, transplant of faecal microbiota was recently shown to promote response in a small number of ICI- refractory melanoma patients [23]. Outcomes from the MITRE study can be expected to inform future strategies for manipulating the patient microbiome with a view to enhancing treatment efficacy in the future.

## Data Availability

Data sharing is not applicable to this article as no datasets were generated or analysed during the current study.

## Abbreviations

AJCC: American Joint Committee on Cancer
ALK: Anaplastic Lymphoma Kinase
ALP: Alkaline Phosphatase
BCG: Bacillus Calmette–Guérin
BMI: Body Mass Index
CCTU-CT: Cambridge Clinical Trials Unit – Cancer Theme
CD4: Cluster of Differentiation 4
CD8: Cluster of Differentiation 8
CFS: Clinical Frailty Scale
CRF: Case Report Form
CRUK: Cancer Research UK
CT: Computerized Tomography
CTCAE: Common Terminology Criteria for Adverse Events
CTLA-4: Cytotoxic T-lymphocyte-associated Protein 4
DNA: Deoxyribonucleic Acid
ECOG PS: Eastern Cooperative Oncology Group Performance Status
EGFR: Epidermal Growth Factor Receptor
CRP: C-reactive Protein
FOXP3: Forkhead Box P3
GGT: Gamma Glutamyl Transferase
GP: General Practitioner
Hb: Haemoglobin
HbA1c: Glycated Haemoglobin
IFNγ: Interferon Gamma
IL-6: Interleukin 6
IrAE: Immune-related Adverse Event
K: Potassium
KPS: Karnofsky Performance Status
LDH: Lactate Dehydrogenase
MRI: Magnetic Resonance Imaging
Na: Sodium
NCI: National Cancer Institute
NIHR: National Institute for Health Research
NSAID: Non-steroidal Anti-inflammatory Drug
NSCLC: Non-small Cell Lung Cancer
OS: Overall Survival
PBMC: Peripheral Blood Mononuclear Cell
PD-1: Programmed Cell Death Protein 1
PD-L1: Programmed Death Ligand 1
PD-(L)1: Programmed Cell Death Protein 1 or Programmed Death Ligand 1
PFS: Progression-free Survival
PPI: Proton Pump Inhibitor
REC: Research Ethics Committee
RECIST: Response Evaluation Criteria In Solid Tumours
RFS: Relapse-free Survival
RNA: Ribonucleic Acid
SARS-CoV-2: Severe Acute Respiratory Syndrome Coronavirus 2
SMG: Study Management Group
SNV: Single Nucleotide Variant
TNFα: Tumour Necrosis Factor Alpha
